### Outcomes

All outcomes and predictor variables will be measured in telephone interviews based on questionnaires developed by the research team at the University of Kassel. Participants (intervention and waiting control group) will be interviewed before the JOBS Program Germany (*t*_*0*_), immediately after the JOBS Program Germany have completed (*t*_*1*_) and 6 months after the JOBS Program Germany have completed (6-months follow-up, *t*_*2*_) (Fig. 1).

#### Primary outcome measures

##### Reintegration into the labor market

Reintegration into the labor market will be assessed using a binary indicator of participants’ current employment status (employed vs. unemployed). For those participants who are employed, we will also assess whether they have a fixed-term or a permanent employment contract as well as their weekly working hours. Any subsided labor market activities (e.g., “Mini-Job”) will be assessed, additionally.

##### Self-esteem and self-efficacy

Participants’ self-esteem is measured with a revised German version of the widely used Rosenberg Self-Esteem Scale [18, 19], for which an internal consistency of Cronbach’s alpha = .84 is reported. Self-efficacy is measured using three short scales for assessing the internal-external control conviction [20], general self-efficacy [21], and generalized self-efficacy expectation [22]. Reliability for the first two scales are reported in terms of McDonald’s omega and lie in the ranges of .53–.73 and .81–.87, respectively. Cronbach’s alpha for the generalized self-efficacy expectation is reported as .74–.94.

##### Health and health-related outcomes with an emphasis on mental health

We assess life satisfaction with a German version of the Satisfaction with Life Scale (SWLS) [23]. A recent study has tested the psychometric properties of the SWLS in a general population survey in Germany [24]. The results confirm that the SWLS is one-dimensional, and indicate measurement invariance across gender and age. Furthermore, satisfaction with life proofed to be associated with fatigue, the mental health component of quality of life, anxiety, dispositional optimism, pessimism, and sleep quality.

We assess participants’ health status by asking for a self-evaluation of their overall state of health (answers on a 5-point Likert-type Item labeled from “very good” to “very bad”). Additionally, we examine whether participants feel restricted in their everyday activities by chronic health problems. Moreover, we use the Patient-Health-Questionnaire 15 (PHQ-15) to assess the severity of somatic symptoms.

Psychological distress is measured with a short, 21-Item version of the depression-anxiety-stress-scale (DASS-21). Psychometric properties of the DASS-21 (e.g., Cronbach’s alpha = .78–.89) have been assessed in Germany [25] and the DASS-21 has been successfully administered via telephone interviews in various countries [26].

Depressive symptoms are measured using the WHO Well-Being Index (WHO-5) and the Patient-Health-Questionnaire 9 (PHQ-9). The WHO-5 consists of five questions, which assess the subjective well-being. A systematic review, including 213 studies, suggests that the WHO-5 is an adequate instrument for screening depressive symptoms in clinical trials [27]. The WHO-5 has also been successfully applied in the German context [28]. The PHQ-9 module consist of 9 items that are specifically designed to assess depression and have been widely used in clinical contexts as well as in research [29]. It has also been shown that result from the self-administered PHQ-9 are comparable to results for the PHQ-9 administered in telephone interviews [30].

#### Secondary outcome measures

The duration of unemployment, job-search intensity, and, if applicable, job satisfaction are collected via telephone interviews at all three occasions (*t*_*0*_, *t*_*1*_, *t*_*2*_, see Fig. 1). We measure job-search specific self-efficacy with a single Likert-type item that assess the likelihood of finding a job. At the baseline (*t*_*0*_), we also assess basic socio-demographic characteristics, such as participants’ age, gender, citizenship, and level of education.

### Sample size

This trial is conceptualized as a confirmatory study. The respective studies in the US and Finland reported small effect sizes (Cohen’s *d*) ranging from about .14 to .32. for self-esteem, self-efficacy, psychological distress, and depressive symptoms [7, 11]. In order to detect effect sizes of .2, which we deem to be of practical relevance, with 85% power and the conventional alpha-level of .05 (two-tailed t-test), we require a sample size of 450 persons per group. This sample size also allows us to detect a 10 percentage points difference in reemployment with 85% power and alpha-level of .05, assuming a reemployment rate of 30% in the waiting control group. To arrive at our target sample size, we aim at recruiting a total of 1500 unemployed, assuming a dropout rate of 60% between the pre-test (*t*_*0*_) and the 6-months follow-up (*t*_*2*_). We further expect about 60% of the unemployed who attend the information event to participate in our study, resulting in an estimated 2500 unemployed who attend an information event. We summarize our assumptions about response rates and panel attrition in Table 1.

**Table 1 Tab1:** Assumptions about number of participants, response rates, and panel attrition

	Information Event	Allocation/Pre-Test	Post-Test	6-months follow-up
	*-t*_*1*_	*t*_*0*_	*t*_*1*_	*t*_*2*_
Response rate (per cent)		60%	80%	75%
Intervention group (n)	2500	750	600	450
Waiting control group (n)		750	600	450
Total (n)	2500	1500	1200	900

Notes: -*t*_*1*_: 4–5 weeks before JOBS Program Germany; *t*_*0*_: pre-test interview and randomization within 1–2 weeks before JOBS Program Germany; *t*_*1*_: post-test interview within 4 weeks after JOBS Program Germany; *t*_*2*_: second post-test interview (follow-up) 6 months after JOBS Program Germany

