## Methods

### Trial design

This confirmatory study is designed as a multi-center, non-blinded, two-armed, parallel-group, randomized controlled trial over 6 months. This design is oriented towards two previous studies from the US and Finland [10, 11]. Participants will be randomly assigned to either an intervention group, who completes JOBS Program Germany right away or a waiting control group, who will not participate in JOBS Program Germany during the trial. The allocation ratio will be 1:1. Primary and secondary outcomes (see below) will be repeatedly assessed at three points in time: (1) immediately before the intervention (*t*_*0*_), (2) immediately after the intervention (*t*_*1*_), and (3) 6 months after the intervention has ended (*t*_*2*_; see: Fig. 1).

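### The sample-size text assumes 60% dropout, but Table 1, the 1500 target and the 450 per group all imply 60% retention, that is 40% dropout

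*Protocol article*

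**What the plan says.** All the relevant statements stand in the Sample size section of the protocol article, apart from the allocation ratio, which is under Trial design.

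- Target for the continuous outcomes: the difference to be found is introduced by "In order to detect effect sizes of .2, which we deem to be of practical relevance". The test is two-sided at alpha 0.05, the power is 85%, and the resulting requirement reads "we require a sample size of 450 persons per group".
- Re-employment: the claim is "This sample size also allows us to detect a 10 percentage points difference in reemployment with 85% power". For the control arm the planning value is given as "assuming a reemployment rate of 30% in the waiting control group".
- Allocation: "The allocation ratio will be 1:1".
- Recruitment and attrition in the text: "we aim at recruiting a total of 1500 unemployed, assuming a dropout rate of 60% between the pre-test". That interview is t0; the interval named in the sentence ends at t2, the final interview.
- Recruitment and attrition in Table 1, which the text presents as the summary of its response and attrition assumptions: response rates of 60% at t0 (from the information event), 80% at t1 and 75% at t2. The counts are 750, 600 and 450 per group, or 1500, 1200 and 900 in total.

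**The concern.** The sentence and the table describe the same interval, t0 to t2, with different losses. The sentence loses 60% of those randomised and the table loses 40%. From 1500 randomised, the sentence leaves 600 participants and the table leaves 900.

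The sentence is the only place where the article gives a dropout rate as such, and it is offered as the reason for recruiting 1500. A reader who takes it at face value cannot get from 1500 to the required 450 per group, and cannot tell whether the planners expect 900 or 600 people at the final interview. Anyone who later compares observed attrition with the plan would have two different planned values to choose from.

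**Working it through.** **Inputs** (Sample size section and Table 1; allocation from Trial design): two-sided alpha 0.05; power 85%; d = 0.2; re-employment 30% versus 40%; 1:1 allocation; 1500 randomised (750 per group); stage response rates 80% and 75%; dropout in the text 60%.

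**1. Reproduce the stated 450 per group.** With the normal approximation, n = 2(z₀.₉₇₅ + z₀.₈₅)² / d² = 2(1.960 + 1.036)² / 0.04, which rounds up to 449 per group. The exact t-test calculation gives 449.9, so 450. The stated figure reproduces. Power at 450 per group is 85.0% (t-test).

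**2. Check the re-employment claim.** For 30% versus 40%, the usual two-proportion formula needs 407 per group (427 with continuity correction). Power at 450 per group is 88.3%, so the claim of 85% is met.

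**3. Retention implied by Table 1.** 0.80 × 0.75 = 0.60 retained, so dropout is 1 − 0.60 = 40%. Counts: 750 × 0.80 = 600 and 600 × 0.75 = 450 per group. The table's rates and counts agree with each other.

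**4. Which dropout rate yields the 1500 target?** Number to randomise = n / (1 − dropout).

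| Dropout t0 to t2 | Per group to randomise for 450 at t2 | Total |
|---|---|---|
| 40% (Table 1) | 450 / 0.60 = 750 | 1500 |
| 60% (text) | 450 / 0.40 = 1125 | 2250 |

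Only 40% gives 1500. The common shortcut of multiplying by (1 + dropout) does not rescue the text either: 450 × 1.6 = 720 per group, 1440 in total.

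**5. Could the 60% refer to another step?** The step from information event to participation is also 60% (2500 × 0.60 = 1500), but the text gives it in a separate sentence and Table 1 in a separate column. The disputed sentence names t0 and t2 as its end points.

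**6. Consequence if 60% loss were really meant.** 750 × 0.40 = 300 per group at t2.

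| Per group at t2 | Power, d = 0.2 (t-test) | Power, 30% vs 40% |
|---|---|---|
| 450 | 85.0% | 88.3% |
| 300 | 68.6% | 72.9% |

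The normal approximation for d = 0.2 at 300 per group agrees: 0.2 × √(300/2) − 1.960 = 2.449 − 1.960 = 0.489, which corresponds to 68.8%.

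**The case against.** The strongest reply is that this is one mislabelled number. The 1500 target, the 450 per group, both stage rates and every count in Table 1 fit 40% dropout, and the text itself names the table as the summary of its attrition assumptions. On that reading nothing in the design changes. This stands, and it decides how the point should be put: as a contradiction to correct, with no shortfall in sample size shown.

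Three stronger readings are tempting, and the documents do not support them.

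- A reader might infer that the trial is underpowered, at about 69% instead of 85%. That follows only if 60% loss is truly expected, and no other figure in the article points that way.
- A reader might treat 69% as the power of the trial as a whole. It applies to an unadjusted two-sample t-test on completers at d = 0.2. The re-employment comparison would have about 73%. The Statistical methods section also plans baseline-adjusted regression, and multiple imputation when more than 5% of values are missing. Neither enters the sample-size calculation, so neither resolves the contradiction, but 69% is not the power of every planned analysis.
- A reader might infer that fieldwork will be judged against the wrong rate. The section on auditing trial conduct lists recruitment, participation rates in the program and the time schedule as monitored items, and sets no attrition benchmark. Whether the figure has been carried into other documents cannot be seen from the article.

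What the reply does not remove is the contradiction itself. The table is legible and consistent within itself, and nothing elsewhere in the article corrects the sentence.

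**Conclusion.** The point holds as an internal contradiction in the Sample size section. The text's 60% dropout from t0 to t2 is incompatible with Table 1, with the 1500 target and with the 450 per group, all of which require 60% retention and hence 40% dropout. The discrepancy is 300 participants at the final interview (900 versus 600).

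The most probable explanation is that retention was written as dropout. If so, the planned 1500 and the 85% power stand. This is an inference from the weight of the other figures; only the authors can confirm it. The power figures of about 69% and 73% are conditional on 60% loss being meant. They rest on the plan's own alpha, effect sizes and 30% control rate, with equal loss in both groups as Table 1 assumes.

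**What to change.** Replace the dropout figure in the text with: *a dropout rate of 40% (60% retained: 80% at t1 × 75% at t2)*. This costs one corrected number. The recruitment target, Table 1 and the power statement stay as they are, and no further participants are needed.

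Only if 60% loss is really expected is more required. Table 1 must then show 300 per group at t2, with stage rates that multiply to 0.40. Power should be restated as about 69% for d = 0.2 (unadjusted t-test on completers) and about 73% for 30% versus 40% re-employment. Keeping 450 per group instead would mean randomising 2250, which is 750 more than planned. At the assumed 60% participation that needs 2250 / 0.60 = 3750 people at information events, against the planned 2500.

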### Data collection and management

The first information events for recruiting participants will take place in March 2021 at four locations. While participants in these four locations follow the regular procedure and time schedule, as described above, the collected data will not be included in the (main) study and will not be part of the analyses. Instead, participants in these first four locations are treated as a pilot sample. This pilot sample will comprise approximately 50 participants who will be allocated to intervention and waiting control groups as described above. The main study is expected to start in April 2021. Participants in the pilot-study will complete JOBS Program Germany (if assigned to the intervention group), the post-test interview (*t*_*1*_), and the 6-months follow-up interview (*t*_*2*_), respectively (Fig. 1), about 1 to 2 months prior to participants of the main study. Questionnaires will be adjusted, if needed, within these 1 to 2 months before being administered to participants of the main study.

Questionnaires are developed by the research team at the University of Kassel, and implemented by SOKO in the CATI software Voxco. The implementation includes automated plausibility checks and filters. Interviews will be conducted by experienced interviewers, who will be trained to administer the specific questionnaires. Interviews will, on average, take 30 min to complete. A detailed methods and field report, including a description of quality assurance measures such as training and supervision of the interviewers, and data processing procedures will be compiled.

The Data will be collected and stored at SOKO, and handled in strict compliance with the German Federal Data Protection Act and the European General Data Protection Regulation (DSGVO). Participants’ contact information will be stored separately from the survey data (i.e., participants’ answers). After data collection, each respondent will be assigned a unique identification code, and the survey data (but not the contact information) will be transferred to the research team at the University of Kassel. Data transfer will be conducted via a secure data exchange server. The entire process of data collection, processing, storage, and backup will be documented in a detailed report.

### Statistical methods

Statistical methods will include t-tests (or equivalent tests for proportions) as well as linear and (binary) logistic regression models. We will compare primary and secondary outcomes between the intervention and waiting control groups.

Reintegration into the labor market (employed vs. unemployed) and the type of contract (temporary vs. permanent) will be assessed using t-tests (or equivalent test of proportions) and logistic regression models. In all analyses, we will treat Likert-Type items as continuous variables. For life-satisfaction, depressive symptoms, and psychological distress, we will first construct (additive) indices. We will then test mean differences in the respective indices between intervention and waiting control groups using t-tests. In multivariate analyses, we will use linear regression models to adjust for baseline-measures of the respective outcomes. Additional models will also adjust for socio-demographic characteristics and indicators of labor market biography, such as the duration of unemployment. We proceed in a similar fashion to analyze self-esteem, self-efficacy and our secondary outcomes job satisfaction and job-search intensity.

To test for potential effect modifications, we include interaction terms between our treatment-indicator and the respective moderators (job-search intensity, duration of unemployment) in the respective regression models.

All multivariate analyses will include controls for socio-demographic variables and (un-)employment history. We will repeat our main analyses stratified by gender. All analyses will be carried out according to the  “intention-to-treat” principle. Participants will be treated as belonging to the group to which they were originally (randomly) allocated. We tolerate low proportions of missing values of up to 5%, and perform listwise-deletion (complete-case analyses). If the proportion of missing values exceeds the predefined threshold of 5%, we will treat missing values by means of multiple imputation [31–33].

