### Specific objectives

The objective of this study is to investigate the effects of the JOBS Program intervention on the reintegration into the labor market, life satisfaction, state of health, depressive symptoms, and psychological distress among the unemployed in Germany. Of secondary interest are moderating factors such as socio-demographic characteristics, the duration of unemployment, and the job-search intensity.

We will compare the reintegration into the labor market and mental health amongst unemployed, who will be randomly assigned to an intervention group that completes JOBS Program Germany, to a waiting control group. The waiting control group will complete JOBS Program Germany only after the trial has terminated.

Given the confirmatory nature of this study, our hypotheses closely resemble those formulated in the respective studies that have investigated the JOBS Program in the US and Finland [10–13]. Compared to the waiting control group, the intervention group is expected to be more often and better reintegrated into the labor market. Moreover, the intervention group is also expected to report higher levels of life satisfaction, to assess its health status more favorably, and to have lower levels of psychological distress and depressive symptoms. More specifically, the following six hypotheses will be tested:

*Hypothesis1*: The JOBS Program Germany will increase the level and quality of reemployment in the intervention group compared to the waiting control group.

*Hypothesis 2*: The JOBS Program Germany will increase self-esteem and self-efficacy and decrease depressive symptoms and distress in the intervention group compared to the waiting control group.

*Hypothesis 3*: The risk of depression, assessed by a high level of depressive symptoms before the JOBS Program Germany, will moderate the effects of the JOBS Program Germany on reemployment and mental health outcomes. The JOBS Program Germany will have stronger employment promoting and mental health effects on those with a higher risk of depression.

*Hypothesis 4*: The job-search intensity, assessed before the JOBS Program Germany starts, will moderate the effects of the JOBS Program Germany on reemployment. The JOBS Program Germany will have stronger employment promoting effects on those with lower initial levels of job-search intensity.

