### Procedure

Due to the country-wide implementation of the JOBS Program Germany in the community-settings, the exact dates of enrollment and trainings will vary across the participating locations. Also, at some locations, more than one JOBS Program Germany will be conducted. However, for any given JOBS Program Germany at a given location, the time schedule is fixed.

Figure 1 shows the time schedule for a typical JOBS Program Germany at a given location. At each of the participating locations and for each JOBS Program Germany there will be an information event for the unemployed. This information event will be scheduled and announced (e.g., via flyer, by agents of the Jobcenters) about 4 to 5 weeks before the JOBS Program Germany starts (−*t*_*1*_). During these information events, two trainers, who will later lead the respective JOBS Program Germany, will explain the intervention and provide participants with a written information sheet that summarizes the objectives, procedure, and contents of the program. Trainers will also address any questions from potential participants. Participation is voluntary and free of charge, and a withdrawal is possible at any time without consequences. At the end of the information events, trainers will obtain written informed consent from the unemployed who are willing to participate.

Following the information event, participants who have given informed consent will be contacted and asked to complete an initial CATI during which participants’ eligibility for the trial is assessed. Participants meet the inclusion criteria if they are between 18 and 65 years old and currently unemployed according to the German Social Code, Book III by the time of the interview. Participants who, by the time of the interview, are full-time students or otherwise inactive on the labour market, and those with insufficient command of the German language to complete the CATI are excluded from the trial.

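### The planned between-arm test of contract type is naturally read as restricted to the employed, a group formed after randomisation by the outcome the programme is meant to change

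*Protocol article*

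**What the plan says.** Hypothesis 1 (Specific objectives) states that the programme "will increase the level and quality of reemployment in the intervention group compared to the waiting control group". At the screening interview, participants must be "currently unemployed according to the German Social Code, Book III by the time of the interview", so any employment seen later arises after allocation.

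Under Primary outcome measures, reintegration is a binary employment indicator. Job characteristics are then added for a subset: "For those participants who are employed, we will also assess whether they have a fixed-term or a permanent employment contract". Weekly working hours are collected from the same subset. Job satisfaction is a secondary outcome, collected where it applies.

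For the analysis, Statistical methods says: "Reintegration into the labor market (employed vs. unemployed) and the type of contract (temporary vs. permanent) will be assessed using t-tests"; the sentence goes on to allow a comparable test of proportions and adds logistic regression. The coding has two categories, and no rule covers people who are still unemployed. The section applies intention-to-treat to all analyses and explains it as follows: "Participants will be treated as belonging to the group to which they were originally (randomly) allocated". For missing data it allows complete-case analysis up to 5%, and otherwise: "If the proportion of missing values exceeds the predefined threshold of 5%, we will treat missing values by means of multiple imputation".

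**The concern.** A between-arm comparison is protected by randomisation only if membership of the analysed set does not depend on treatment. Here it would depend on being employed at the interview, which Hypothesis 1 and the Sample size section both expect the programme to change. If the programme brings additional people into work, the employed in the intervention arm include people with no counterpart among employed controls. Those people may find different kinds of jobs. The test then mixes any effect on job quality with a change in who is employed. A programme that places harder-to-place people in fixed-term jobs could appear to worsen job quality although nobody's job got worse; the reverse is equally possible.

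What is at stake is the reading of the quality part of Hypothesis 1. The employed-versus-unemployed comparison in the same sentence is defined for everyone and is not affected.

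**Working it through.** **Inputs from the protocol (Sample size and Table 1).** Two-sided alpha 0.05, power 85%, d = 0.2, re-employment 30% in controls with a 10-point difference (so 40%), 750 per arm allocated and 450 per arm expected at 6 months.

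**Assumptions, not in the protocol.** The permanent share of control jobs is 50% (range 40% to 60%). The permanent share of the jobs that exist only because of the programme is 10% to 80%. The programme puts nobody out of work and does not change the contract of anyone who would be employed anyway.

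**The plan's own figure.** n per arm = 2(1.960 + 1.036)²/0.2² = 449 by normal approximation, and 450 with the t distribution. This matches the stated 450. At 450 per arm, 30% against 40% has 88.3% power, so the re-employment statement also holds. No sample size is given for contract type.

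**People with a contract type.** Controls: 450 × 0.30 = 135. Intervention: 450 × 0.40 = 180. Of the employed in the intervention arm, 10 of 40 points, or one quarter, are additional.

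**Spurious difference.** With permanent share p in control jobs and q in the added jobs, the intervention share among the employed is (0.30p + 0.10q)/0.40. The difference from controls is therefore (q − p)/4. The chance of rejection at nominal 5% uses the normal approximation with SE = √[p(1−p)/135 + p₁(1−p₁)/180], where p₁ is the intervention share. For p = 50%:

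| q | Permanent among employed, control vs intervention | Difference (points) | Rejected | Permanent employment among all followed up |
|---|---|---|---|---|
| 10% | 50% vs 40% | −10 | 42.5% | 15% vs 16% |
| 20% | 50% vs 42.5% | −7.5 | 26% | 15% vs 17% |
| 30% | 50% vs 45% | −5 | 14% | 15% vs 18% |
| 50% | 50% vs 50% | 0 | 5% | 15% vs 20% |
| 80% | 50% vs 57.5% | +7.5 | 26% | 15% vs 23% |

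For example, at q = 20%: SE = √(0.25/135 + 0.425 × 0.575/180) = 0.0567, and 0.075/0.0567 = 1.32, which gives 26% rejection. With p between 40% and 60%, the spurious difference ranges from −12.5 to +10 points.

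**Power of the employed-only test.** For a 10-point difference at 135 against 180, power is 42% to 46% for control shares of 40% to 60%. A difference of about 16 to 17 points is needed for 85%.

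**Power of the outcome defined for everyone.** At 450 per arm and the same contract mix in both arms: 12% vs 16% gives 41%, 15% vs 20% gives 51%, and 18% vs 24% gives 60%. At 15% vs 18% it is 23%. In the table above, only the row with 80% permanent among the added jobs passes 85% (15% vs 23%, 86.5%).

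**Missing-data rule.** Among those followed up, 70% of controls and 60% of the intervention arm have no contract type because they have no job. That is far above the 5% threshold, so a literal application would impute contracts for unemployed people.

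**The case against.** - **The restriction to the employed is inferred.** The protocol never says that the test is among the employed, and a condensed article may leave the analysis set to the full plan. This is fair as far as it goes. But the article does fix a two-category variable, collects it only from the employed and names the test, so no other reading is as direct.
- **Covariate adjustment.** Logistic models with socio-demographic and employment-history controls are planned. They may reduce selection, but they cannot be relied on to remove it, and the unadjusted test has no such help.
- **Conflict with intention-to-treat.** A reader might infer that the plan contradicts its own intention-to-treat statement. It does not: the protocol defines the principle as analysis by allocated group, and an employed-only comparison by allocated arm complies with that wording.
- **Weight in Hypothesis 1.** A reader might also infer that half of the hypothesis rests on this test. The documents do not support that. The reintegration indicator is binary employment status, the sample size addresses only that difference for reintegration, and contract type is assessed in addition. Statistical methods names no between-arm test of weekly hours.
- **The magnitude rests on assumed shares.** This stands. With equal shares there is no bias, and the illustrative 50% vs 45% would reach significance only about 14% of the time.
- **The remedy answers a different question.** This also stands. With job quality unchanged (50% in both arms), the recoded outcome still gives 15% vs 20%, purely from the extra jobs.

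**Conclusion.** The concern holds in a limited form. As naturally read, the contract-type test conditions on a post-randomisation outcome and can mislead about job quality in either direction. With the protocol's 30% and 40%, 50% permanent among control jobs and 10% to 80% among added jobs, the spurious difference is −10 to +7.5 points, with rejection up to about 42.5% at nominal 5%. It is zero if the added jobs have the same mix as control jobs. The contract shares and the absence of negative effects on employment are assumptions, so neither size nor direction can be derived from the protocol.

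The figures of 135, 180 and 450 refer to people followed up at 6 months, not to the 750 allocated per arm, and they ignore differential dropout. The stated sample size and the main employment comparison are not in question. This should be changed before analysis, but it does not undermine the trial.

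**What to change.** Make the between-arm test one that is defined for everyone allocated, with non-responders handled by the plan's missing-data rule:

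- permanent employment yes/no, with not employed counted as no; or an ordered outcome, not employed < fixed-term < permanent;
- if weekly hours are compared between arms, not employed set to 0;
- contract type and job satisfaction among the employed reported by arm as descriptive only, without a between-arm test;
- a statement that the missing-data rule covers non-response, and that the absence of a contract in an unemployed person is not a missing value.

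The plan should also state the downside. The recoded outcome combines level and quality of re-employment, so a difference on it must not be read as an effect on job quality alone. A reader might expect the larger denominator to restore power; at an equal contract mix it gives only 41% to 60% at 450 per arm.

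The cost is a change of wording and a recoding of variables already collected. No further data are needed.
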